## Abstract

**Introduction:**

Functional neurological disorder (FND) refers to an involuntary loss of control over and/or aberrant perception of the body. Common presenting symptoms are functional (non-epileptic) seizures, and functional motor disorder, for example, walking difficulties, weakness or tremor. Greater access to effective treatments would lead to reduced distress and disability; and reduce unnecessary healthcare costs.

This study will examine eye-movement desensitisation and reprocessing therapy (EMDR) as a treatment for FND. EMDR is an evidence-based treatment for post-traumatic stress disorder (PTSD), but its use for other conditions is growing. An FND-specific EMDR protocol will be tested, and if the intervention proves feasible with promising clinical outcomes, progression to a substantive study could take place.

**Methods and analysis:**

Fifty adult patients diagnosed with FND will be recruited. It will be a single-blind randomised controlled trial with two arms: EMDR (plus standard neuropsychiatric care; NPC) and standard NPC. The two groups will be compared at baseline (T0), 3 months (T1), 6 months (T2) and 9 months (T3). Measures of feasibility include safety, recruitment, retention, treatment adherence and acceptability. Clinical outcome measures will assess health-related functioning/quality of life, ratings of FND symptoms and severity, depression, anxiety, PTSD, dissociation, service utilisation and other costs. Improvement and satisfaction ratings will also be assessed. Feasibility outcomes will be summarised using descriptive statistics. Exploratory analyses using (linear/logistic) mixed-effect models will examine the rate of change in the groups’ clinical outcome measures across the four time-points.

After the intervention period, a sample of participants, and clinicians, will be invited to attend semistructured interviews. The interviews will be analysed using reflexive thematic analysis.

**Ethics and dissemination:**

This study has been approved by the NHS West Midlands—Edgbaston Research Ethics Committee. Study findings will be published in open access peer-reviewed journals, presented at conferences, and communicated to participants and other relevant stakeholders.

**Trial registration:**

NCT05455450 (www.clinicaltrials.gov).

Strengths and limitations of this studyThis is a pragmatic randomised controlled trial embedded within an existing clinical service.The eye-movement desensitisation and reprocessing therapy is tailored for functional neurological disorder presentations.There has been patient and public involvement (PPI) input from the design stage, and there is continued PPI involvement.The study will use a validated self-report measure to assess post-traumatic stress disorder, rather than a clinical interview.

## Introduction

Functional neurological disorder (FND) is a disorder at the interface between neurology and psychiatry. It refers to an involuntary loss of control over and/or aberrant perception of the body. Presenting symptoms can be wide ranging with the most common being functional (non-epileptic) seizures (FS) and functional motor disorder (mFND), for example, walking difficulties, weakness, tremor. Risk and perpetuating factors for FND include traumatic experiences, affective disorders and experiencing chronic or acute illness. FND is one of the most common diagnoses made in neurology, for example, 16% of new patients in general neurology^1^; causes similar disability and impairment in quality of life as Parkinson’s disease and multiple sclerosis, and high unemployment.^2^ Lack of provision of assessment and treatment is associated with significant unnecessary costs, for example, unnecessary referrals, investigations, and emergency department attendances.^3 4^

Accessing treatment is often difficult, and effective treatments for FND are still being established. Healthcare Improvement Scotland published guidance in 2012, recommending a stepped-care approach, whereby patients are assessed and diagnosed by a neurologist, and referred for relevant interventions (eg, physiotherapy, psychology, psychiatry, occupational therapy) as required.^5^ A cornerstone of FND treatment is effective communication of the diagnosis, and guidelines regarding management of FND have been published.^6 7^ There have been consensus recommendations published for physiotherapy for mFND and occupational therapy.^8 9^ The best evidence for mFND specifically comes from a feasibility study evaluating a specialist physiotherapy intervention compared with physiotherapy in the community, which reported positive outcomes in terms of recruitment, retention, acceptability and clinically meaningful effect sizes.^10^ A multicentre NIHR-funded randomised controlled trial (RCT) evaluating this is underway (International Standard Randomised Controlled Trials Number ISRCTN56136713). However, this intervention is not suitable for a large proportion of patients with mFND (only 32% of eligible patients met the inclusion criteria; most common reasons for exclusion were dominant persistent pain and psychological factors requiring treatment). There have been reports of beneficial outcomes following cognitive behavioural therapy (CBT) in uncontrolled studies for patients with mFND, but no controlled and adequately powered studies have been carried out.^11^ For FS specifically, the multicentre CODES trial compared CBT plus standard medical care (SMC) to SMC alone. Although this study did not find a significant difference in monthly seizure frequency between the groups, they did find significant improvements for CBT on secondary measures (psychosocial functioning, psychological distress and health-related quality of life).^12^ Previous studies evaluating CBT for FS have reported significant improvements in seizure frequency.^13 14^ More research regarding effective psychological treatments other than CBT for FND is needed, to inform delivery of treatment.

Cross-sectional studies suggest that lifetime traumatic/adverse experiences are higher in FND populations, when compared with healthy controls; in particular for those with FS, who also have higher incidences of post-traumatic stress disorder (PTSD).^15^ The occurrence of severe life events immediately prior to symptom onset is significantly more frequent in those with mFND compared with psychiatric controls^16^ and it has been proposed that there is a trauma subtype of FND.^17^ Traumatic/adverse life events, including physical events such as injury or illness, are a risk factor and can be a trigger for developing FND. Mechanistic models of FND have been developed focusing on different levels of explanation from the neurobiological to the psychosocial. Neurobiological models have used predictive coding models of perception and movement control to suggest that symptoms in FND relate to the development of abnormal priors which are activated by misdirected attention towards the body.^18^ This links closely with cognitive models suggesting that learnt patterns of behaviour are triggered by abnormal threat processing.^19^ Emotional dysregulation, abnormal interoceptive processing and alexithymia can all be integrated with such models, building a complex picture of the biological and psychological processes that underpin FND.^20^ This provides a scientific foundation for the development and application of specific psychological interventions to treat people with FND.

Eye-movement desensitisation and reprocessing therapy (EMDR) is an evidence-based treatment for PTSD, but its use for other conditions is growing, including treatment of somatic symptoms such as persistent pain and tinnitus.^21–24^ EMDR follows a standard protocol (see table 1).^25^ Within EMDR, a target memory is brought to mind, while the clinician creates a distracting task that means the person’s attention is divided between the memory and the present-focused task. Traditionally, eye-movements are used, but other tasks that create dual attention can be used, for example, tapping. The working memory (WM) hypothesis suggests that focusing on the memory, while engaging in a competing task, results in the memory becoming less vivid and distressing. A recent systematic review, identifying 11 studies testing the WM hypothesis, concluded that bringing a distressing memory to mind, while engaging in a secondary task, results in reduced vividness and emotionality of the memory, and is associated with symptom reduction.^26^

**Table 1 T1:** The eight phases of EMDR according to the standard protocol (Shapiro 2018)

Phase	Description
I–II	Taking of patient history, assessment of suitability for EMDR and preparation for the therapy.
III	Assessment of a target image whereby the patient is asked to bring a target memory to mind, identify the most upsetting image or moment and identify the negative cognition about themselves that goes with that moment. They are also asked to identify a positive cognition and rate their belief in that cognition. Additionally, they are asked to rate their subjective distress, identify the associated emotions and locate where they feel the distress in their body.
IV	Desensitisation phase: the patient is asked to bring the target memory to mind, with the negative cognition, notice where they are feeling the distress in their body and follow the clinician’s fingers with their eyes (or other alternating task that taxes working memory). After each set of eye movements, the patient is asked what they noticed, and importantly, without discussion, they are told to ‘go with that’ alongside the eye movements. Once the distress has reduced sufficiently (this may involve multiple sessions), the clinician proceeds to the installation phase.
V	Installation phase: positive cognition is installed, aided by eye-movements (or alternative).
VI	Target any remaining distress in the body.
VII	Closure of the session.
VIII	Assess previously targeted material and whether or not further processing is required.

EMDR, eye-movement desensitisation and reprocessing therapy.

A systematic review of EMDR as a treatment for FND reported three case studies/series with all five cases presented having comorbid PTSD, of which four cases were successfully treated.^27–30^ EMDR has been reported as a useful adjunctive therapy for two FND cases without PTSD, whereby both cases achieved resolution of FND symptoms and less distress.^31^ EMDR can focus on specific past adverse experiences that are contributing to pathology, memories associated with when FND symptoms began, current FND symptoms and future predictions regarding symptoms. Theoretically, targeting distressing memories/images associated with FND could weaken cognitive representations of symptoms, and reduce threat associated with symptoms, meaning that representations of the symptoms are less easily triggered, resulting in fewer symptoms and less distress. EMDR is a therapy that can be tailored to the heterogeneous presentations of FND.

This study aims to evaluate the feasibility and acceptability of conducting a full-scale trial of EMDR for people diagnosed with FND. Feasibility will be assessed by examining recruitment rate, intervention adherence and retention. Acceptability will be examined through attendance rates, satisfaction ratings, therapy fidelity ratings and qualitative interviews with participants and treating therapists. Assessment of safety across the two arms will be compared. Examination of the completeness of outcome measures and variance in outcomes will be used to inform the design and power calculation of a future definitive trial.

### Study objectives

Test the acceptability and feasibility of an FND-specific EMDR intervention protocol, delivered in-person or virtually. For a substantive RCT, the intervention will be subject to amendment based on the results of this trial.Investigate the value of a range of outcome measures, to determine the outcome measure with greatest effect size to enable a sample size calculation for a substantive RCT.Carry out semistructured interviews with participants and therapists to explore experiences of EMDR and the trial; informing the intervention and design of a substantive trial.

## Methods and analysis

This protocol is reported in accordance with the Standard Protocol Items: Recommendations for Intervention Trials 2013 statement.^32^

### Study design

This feasibility study is a single-blind RCT with two arms: EMDR (plus standard neuropsychiatric care (NPC)) and standard NPC only. The two groups will be compared at baseline (T0), 3 months (T1), 6 months (T2) and 9 months (T3). Fifty adult patients with a diagnosis of FND, confirmed by a neurologist according to standardised diagnostic criteria, will be recruited via a UK neuropsychiatry service. The research assistant (RA) and project statistician will be blind to treatment allocation. After the intervention period, semistructured interviews will be carried with a proportion of participants and clinicians to explore their experiences and views about the trial.

### Study setting

This is a single-site study being carried out at a neuropsychiatry service, based at St. George’s Hospital, Tooting, London, UK. The service is part of the South-West London and St. George’s Mental Health NHS Trust (SWLSTG).

### Public and patient involvement (PPI)

The research design has been informed by a PPI meeting (June 2020), where all five participants had lived experience of FND. Three PPI representatives join regular Trial Management Group (TMG) meetings, review participant literature and will coproduce the interview schedules and contribute to the design of a substantive study. Two PPI representatives join the Trial Steering Committee (TSC).

### Eligibility criteria

#### Inclusion criteria

Predominant diagnosis of FS and/or mFND, with diagnosis confirmed by neurologist.Aged 18 years or over.Capacity to consent.Willingness to attend regular psychological therapy sessions.Reporting at least one traumatic event on the International Trauma Exposure Measure (ITEM).

#### Exclusion criteria

Non-English speaking.Current ongoing adversity that is likely to interfere with psychological therapy, for example, domestic violence, homelessness, unresolved compensation claim/litigation.Predominant diagnosis of borderline personality disorder (comorbid diagnosis is acceptable, as long as FND is the predominant difficulty).Predominant diagnosis of chronic pain condition (comorbid diagnosis is acceptable, as long as FND is the predominant difficulty), for example, fibromyalgia.Predominant diagnosis of chronic fatigue syndrome (comorbid diagnosis is acceptable, as long as FND is the predominant difficulty).Diagnosis of a psychotic disorder.Diagnosis of dissociative identity disorder or score in clinical range on ‘identity disturbance’ subscale of Multiscale Dissociation inventory.Uncontrolled epileptic seizures.Diagnosis of an eating disorder.Current severe self harm or strong suicidal ideation that requires secondary care mental health services input.Current alcohol or drug harmful use or dependence.Current diazepam use exceeding the equivalent of 10 mg per day.Currently attending individual psychological therapy focused on FND or other specialist FND-specific treatment such as inpatient/outpatient multidisciplinary treatment or intensive FND-specific physiotherapy.

### Study interventions

#### EMDR plus standard NPC

The intervention group will be offered up to 16 EMDR sessions, and a 1-month follow-up session, as well as attending standard outpatient neuropsychiatric appointments. Participants will be given the choice of attending EMDR face-to-face or virtually via a video-consultation platform. Sessions will normally be attended weekly, with treatment completed within 6 months. Sessions will be 60–90 min long, in accordance with NICE guidance for PTSD.^33^ A minimum of eight sessions was chosen based on patient feedback and previous research.^34^ Optimum session duration and number will be examined as part of the trial. The optional follow-up session will occur 1 month after treatment completion.

EMDR for FND is a collaborative and individualised approach, following the standard EMDR protocol, but tailored for FND presentations. Treatment has three broad stages: assessment, psychoeducation, target selection and preparation for processing; processing of targets; and ending of therapy. The initial sessions incorporate education regarding FND, anxiety and dissociation; formulating collaboratively with the participant regarding the development of FND symptoms; and giving a rationale for EMDR. In collaboration with the participant, target memories/images will be chosen, such as: (1) distressing memories associated with the time when symptoms began; (2) distressing memories from past events that may be relevant to their FND symptoms; (3) FND symptoms themselves, when present in session, or an image of them; and (4) distressing images about the future, for example, image of having symptoms in front of others. EMDR therapy will follow the therapy protocol developed by the Chief Investigator (CI) for this study. Table 2 shows an overview of treatment, with a guide regarding how many sessions per stage.

**Table 2 T2:** Overview of EMDR for FND

Session(s)	Overview of content
1–3	History taking and preparation for therapy (phase I–II of standard EMDR protocol) Formulating their FND presentation and increasing their understanding of FND Collaboratively selecting target memories/images
4–15*	Processing of EMDR targets using EMDR’s three-pronged approach of past, present and future targets
Final session	End therapy
	An optional follow-up session can be offered 1 month after completing therapy (this does not count as one of the 8–16 sessions)

*Total number of sessions can be between 8–16. If completing by session 8, there will be fewer sessions in this phase of the intervention.

#### Standard NPC

NPC is treatment-as-usual and will consist of 1–3 routine outpatient appointments with an assigned neuropsychiatrist in the trial period. Participants will not begin any FND-specific individual psychological therapy, inpatient/outpatient multidisciplinary treatment or intensive specialist FND-specific physiotherapy. If a participant begins FND-specific individual psychological or physiotherapy treatment in the trial period, they would not be able to complete the trial. Data from their last assessment point will be used for analysis. Participants can still attend psychoeducational interventions focused on FND that are administered by the service and remain part of the trial. Their assigned neuropsychiatrist can refer for psychological therapy outside of the service for any comorbid conditions, for example, therapy for depression.

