### Analysis and statistical methods

#### Sample size

This is a feasibility trial; as such, a power calculation is neither possible nor necessary. Rather, the sample size is pragmatic. Target recruitment is 50 patients in total (25 in each arm), which is consistent with those recommended for pilot and feasibility studies to provide sufficiently reliable estimates of feasibility outcomes, for example, recruitment, adherence and attrition rates and adequate precision of means and variances to inform a fully powered RCT.^39–41^

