Baseline characteristics will be reported according to treatment arm. Continuous variables will be reported as mean (SD) if normally distributed or median (interquartile range) if non-normal, while categorical variables will be presented as frequency (%). Subsequent analyses will summarise the proposed patient-reported and clinical outcomes (eg, quality of life and depression measures, (2-week mean) EMA symptom ratings) at each time point for each trial arm using appropriate descriptive statistics (eg, group mean, SD). To provide an indication of potential changes in scores/frequencies between the four time points, linear/logistic mixed-effects regression models will be employed performed on an intention-to-treat basis (accounting for data assumed to be missing at random). These random intercept (mixed) models will include intervention group, time and intervention group-by-time interaction. There will be no emphasis on hypothesis testing, however, which is reserved for the future main trial. Rather, pre-to-postintervention standardised effect sizes (Hedges’ g, relative risk) will be computed (SDs will be computed from estimated model standard errors) with associated CIs calculated to explore imprecision around effect sizes (Durlak 2009).^43^ Due to the small sample size, important covariates (eg, baseline score on relevant measure, gender, age) may be included in models if the two arms happen to be highly imbalanced. Additional analyses (using mixed effect models) focused on ‘per-protocol’ outcomes and the potential value of the (intensively) collected EMA data on FND symptoms will also be administered (see online supplemental material for additional detail).

A descriptive assessment of healthcare utilisation stratified by treatment arm will also be presented. The Adult Service Use Schedule (AD-SUS) will be used to record previous 6 months of health and social care resource use at baseline (T0) and 9 months of health and social care resource use at 9 months (T3). The acceptability of the AD-SUS will be assessed and key items of resource use for a future RCT will be identified. EQ-5D-5L utility scores will also be calculated. A cost-effectiveness analysis will not be conducted.

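### Starting other FND-specific treatment ends follow-up, which sits badly with the intention-to-treat analysis, and the last-assessment sentence does not say how the data enter the mixed model

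*Protocol article*

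**What the plan says.** The section Standard NPC (under Study interventions) sets the rule for a participant who begins individual psychological therapy or physiotherapy aimed at FND during the trial, and gives the data consequence: "they would not be able to complete the trial. Data from their last assessment point will be used for analysis". The rule stands under the NPC heading but is worded for any participant.

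The Statistical analysis plan section describes the analysis differently: "linear/logistic mixed-effects regression models will be employed performed on an intention-to-treat basis (accounting for data assumed to be missing at random". On the form of the model it says: "These random intercept (mixed) models will include intervention group, time and intervention group-by-time interaction". There are four assessments (Study design): "The two groups will be compared at baseline (T0), 3 months (T1), 6 months (T2) and 9 months (T3".

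Three other places bear on the point:

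- Table 3 makes completion of outcome measures a critical feasibility outcome, with above 70% needed to proceed unmodified. It also collects withdrawal rates in both arms and the reasons.
- The Statistical analysis plan section will consider differential dropout and adds a per-protocol analysis.
- Study objectives says the effect sizes will be used to select an outcome measure and size the main trial.

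**The concern.** An intention-to-treat analysis follows people as randomised, whatever treatment they go on to receive. Here a treatment event after randomisation ends participation, so the outcomes that such an analysis needs are not collected. What remains rests on the missing-at-random assumption, applied to people who leave because they obtained other treatment for the condition under study.

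The event is plausibly linked to poor progress and plausibly more frequent under NPC. Everyone enrolled was willing to attend regular psychological therapy (Inclusion criteria) and participants know their allocation (Blinding). One arm is offered up to 16 EMDR sessions, the other 1 to 3 routine appointments. This is inference; the protocol reports no switching rates.

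Two things are at stake. One is the set of effect sizes that will plan the main trial. The other is the completion rate, which the rule itself lowers, whether or not the participant would have gone on answering questionnaires.

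**Working it through.** The protocol states no figure that depends on this rule, so there is none to reproduce. The check has three parts.

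**1. The two sections side by side.**

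| Reading of the last-assessment sentence | Fit with the missing-at-random mixed model | Outcomes after the switch |
|---|---|---|
| The last value stands in for later visits | Conflicts: the model uses each observed visit and needs no filled-in value | Lost |
| All visits up to the last one are kept | No conflict | Lost |

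The two readings differ in the second column only.

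**2. Completion criterion.** From Sample size: "Target recruitment is 50 patients in total (25 in each arm".

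- 35/50 = 70%, which is not above 70%; 36/50 = 72%, which is. At most 50 − 36 = 14 participants can be lost.
- Each participant removed before T3 costs 1/50 = 2 percentage points.
- Illustration with assumed switching of 30% in NPC and 10% in EMDR: 0.30 × 25 + 0.10 × 25 = 10 participants, or 20 percentage points and 10 of the 14 permitted losses.

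**3. Possible bias in the T0-to-T3 difference (large-sample simulation; every input is an assumption).** Outcome SD 1, lower is better, within-person correlation 0.6, true difference −0.40 SD, switching after T1. The other therapy has no effect or an effect of −0.5 SD at T3. Switching is driven by a poor observed T1 score or by an unobserved worsening trajectory.

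| Driver of switching | NPC/EMDR switching | Effect of other therapy | Follow-up continued | Last value carried forward | Mixed model, visits before switch |
|---|---|---|---|---|---|
| Observed T1 | 20%/5% | 0 | −0.398 | −0.466 | −0.398 |
| Observed T1 | 20%/5% | −0.5 | −0.321 | −0.464 | −0.395 |
| Observed T1 | 30%/10% | 0 | −0.402 | −0.464 | −0.403 |
| Observed T1 | 30%/10% | −0.5 | −0.307 | −0.467 | −0.407 |
| Unobserved trajectory | 20%/5% | 0 | −0.400 | −0.377 | −0.348 |
| Unobserved trajectory | 20%/5% | −0.5 | −0.326 | −0.377 | −0.348 |
| Unobserved trajectory | 30%/10% | 0 | −0.400 | −0.371 | −0.335 |
| Unobserved trajectory | 30%/10% | −0.5 | −0.305 | −0.376 | −0.338 |

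- Largest gap from continued follow-up with carry-forward: 0.467 − 0.307 = 0.16 SD, overstating EMDR.
- Largest gap with the mixed model on visits before the switch: 0.407 − 0.307 = 0.10 SD, also overstating EMDR.
- When the other therapy has no effect and the trajectory drives switching, both understate EMDR: by 0.400 − 0.371 = 0.03 SD (carry-forward) and 0.400 − 0.335 = 0.07 SD (mixed model).
- With equal 10%/10% switching, carry-forward moves the estimate by about 0.02 SD and the mixed model by almost nothing.

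A second set of assumptions has no true effect, 0.3 SD improvement in both arms by T3, the more severe NPC participants leaving after T1, and T1 carried to T3. The spurious EMDR benefit is about 0.07 SD if 10% of NPC leave, 0.12 to 0.13 SD if 20% leave and 0.16 to 0.17 SD if 30% leave. A tighter link between T1 severity and leaving would raise these figures.

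For scale, the 95% CI half-width for a standardised difference with 25 per arm is 1.96 × √(2/25) = 0.55 SD.

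**The case against.** The strongest reply is that nothing here contradicts itself. A reader might infer that the plan prescribes last observation carried forward, but the protocol neither names it nor says that the last value fills T2 or T3. Read with the analysis section, the sentence may simply mean that data already collected are kept, and a mixed model handles that properly. In the simulation, when switching depends on observed T1 scores and the other therapy has no effect, the mixed model shows no bias.

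A reader might also infer that NPC participants receive no therapy for nine months and will therefore leave in numbers. The documents do not support this: NPC includes neuropsychiatric appointments, and participants may attend the service's FND psychoeducation and be referred for therapy for comorbid conditions.

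Further, withdrawals and their reasons are already collected by arm, differential dropout will be considered, hypothesis testing is not emphasised, and any plausible bias lies well inside the sampling error.

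Much of this stands: carry-forward is one reading, and informative switching is plausible but not shown. What remains is that removing participants loses their outcomes after the switch under either reading. Reporting reasons for withdrawal does not recover those outcomes. If the other therapy works and switching is unequal, neither approach recovers the as-randomised difference in most of these scenarios. The lost completers also count against a critical feasibility outcome.

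**Conclusion.** The concern holds in limited form. Ending follow-up at a post-randomisation treatment event sits badly with the stated intention-to-treat analysis, and the last-assessment sentence leaves open how these participants enter the model.

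The certain effect is on completion: 2 percentage points per participant removed before T3, with at most 14 losses allowed. Nothing in the protocol indicates that this rule alone would cause the threshold to be missed.

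The effect on the exploratory effect sizes is uncertain in size and direction. It reaches about 0.17 SD only with carry-forward and assumed switching of up to 30% in NPC. It would be tempting to say that the rule biases the comparison towards EMDR. That does not follow, because the direction depends on what drives switching, whether the other treatment works, and whether the target is the difference as randomised or the difference had nobody switched. An understatement of variance has not been shown either.

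This should be fixed, but it does not undermine the trial: the primary outcomes are feasibility measures and the effect sizes carry a half-width of about 0.55 SD. The reason to act is that outcomes not collected after a switch cannot be recovered later, and the article reports the trial as ongoing.

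**What to change.** Leave the care rule as it is and separate it from data collection:

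- State that starting other FND-specific treatment does not end outcome collection, and continue the scheduled T1 to T3 assessments.
- Record the date and type of that treatment, and report its frequency by arm alongside the withdrawal data already planned.
- Enter all observed visits in the mixed model as randomised, with nothing carried forward.
- Replace the last-assessment sentence under Standard NPC with wording that matches the Statistical analysis plan section.
- Use the per-protocol analysis already planned for data before the switch.
- If a participant declines further follow-up, keep their observed visits in the model.

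The cost is a short wording amendment and a few more of the questionnaires already scheduled. No new visits are needed.
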